##### Inclusion criteria

2.3.2.1

1.Males and females aged between 50 and 75 years.2.Participants diagnosed with MND based on the diagnostic and statistical manual of mental disorders-5 diagnostic criteria.3.Participants with MoCA-K score of 22 or less.4.Participants who have a level of education of more than 6 years (more than elementary education level).5.Participants or authorized surrogates who voluntarily sign the clinical trial consent form.

##### Exclusion criteria

2.3.2.2

1.Alzheimer disease, vascular dementia, Parkinson disease, Huntington disease, hydrocephalus, etc.2.Patients who have had major psychiatric disorders such as schizophrenia, delusional disorder, bipolar disorder, alcohol, or substance abuse disorder, were diagnosed according to diagnostic and statistical manual of mental disorders-5 diagnostic criteria.3.Patients who have had other neurologic diseases such as epilepsy, brain injury, stroke, etc.4.Patients who have participated in other interventional clinical trials for 1 month before the start of the trial.5.Patients who have performed the diagnostic test of cognitive impairment 3 months before the start of the trial.6.Patients who are pregnant, lactating, or not using appropriate methods of contraception.7.Patients with unstable medical conditions (investigators will judge these conditions according to the standard work procedure, based on the results of vital signs, clinical pathology, electroencephalography (EEG), and chest radiography, etc).8.Patients with hypertension, as defined by a systolic blood pressure above 160 mm Hg, or diastolic blood pressure above 95 mm Hg.9.Patients who had clinically significant liver disease or had serum aspartate aminotransferase, alanine aminotransferase, and/or gamma-glutamyl transpeptidase values more than twice the laboratory test upper limit reference.10.Patients who cannot be measured by fNIRS.11.Patients who disagree with acupuncture treatment.12.Patients assessed as ineligible to participate in the trial by the principal investigator for any other reason.

### Study procedure

2.4

All consenting participants will be subjected to the measurement of vital signs (blood pressure, pulse rate, body temperature), demographic information survey, medical history (past, present, family), physical examination, laboratory tests, and electrocardiogram tests. Eligible participants who meet the inclusion and exclusion criteria will receive a schedule of visits (screening).

At visit 1, the investigator will check the subject's vital signs and test ADAS-cog, K-BDI, BAQ, DMTS (response and accuracy), and fNIRS (Oxy-Hb, deOxy-Hb). The control group will receive acupuncture treatment for 30 minutes, while measuring a simple EEG with NF, and the intervention group will receive acupuncture for a minute while performing the NF training protocol (5 times for 5 minutes, 30–60 seconds of rest between each trial). In the meantime, the investigator will check the subject's BPM and HRV. The investigator will check the subject's adverse reactions and concomitant medications and inform them that cigarettes and caffeine must be avoided 2 hours before the test, as they affect the HRV. From visits 2 to 24, both groups will be treated in the same manner as visit 1, and BPM HRV will be checked in the meantime. The investigator will check the subject's adverse reactions and concomitant medications and inform them in the same manner as on visit 1. At visit 24, the investigator will check the subject's vital signs and test ADAS-cog, K-BDI, BAQ, DMTS (response and accuracy), and fNIRS (Oxy-Hb, deOxy-Hb). Additional visits may be performed at any time if deemed necessary by the investigator's judgment, or following the subject's request. In the event of an unexpected visit, the following tests will be performed: vital signs, checking adverse reactions or concomitant drugs, and laboratory tests. In principle, administration of concomitant drugs will be prohibited during the trial, and when combination therapy may occur, it will be decided whether or not to drop out or exclude at the discretion of the principle investigator (PI). A detailed outline of the schedules is shown in Table 1.

**Table 1 T1:** Schedule of trial visits.

	Study period				
Visit	Screening	1	2 to 24	25	UV
Informed consent	О				
Eligibility screen	О				
Demographic information	О				
Drug history	О				
Medical history	О				
Vital signs	О	О	О	О	О
Laboratory test	О				Δ
EKG	О				Δ
MoCA-K	О			О	
ADAS-cog		О		О	
K-BDI		О		О	
BAQ		О		О	
HRV		О	О	О	
Breath signal of neurofeadback		О	О		
Delayed matching to sample task		О		О	
fNIRS		О		О	
Combined treatment		О	О		
Single treatment		О	О		
Check adverse effects		О	О	О	О
Check concomitant drugs		О	О	О	О
Education of visit schedule	О	О	О	О	О

ADAS-cog = Alzheimer Disease Assessment Scale–Cognitive Subscale, BAQ = body awareness rating questionnaire, EKG = electrocardiogram, fNIRS = functional near-infrared spectroscopy, HRV = heart rate variability, K-BID = Korean version of Beck Depression Inventory, MoCA-K = Korean version of Montreal Cognitive Assessment, UV = unexpected visit.

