#### Secondary outcomes

2.9.2

ADAS-cog, K-BDI, BAQ, fNIRS, DMTS, BPM, and HRV will be the secondary outcomes. Endpoints will include the change in ADAS-cog, K-BDI, BAQ, DMTS scores, and fNIRS values from visit 1 to visit 25; HRV values from visit 1 to visit 5, 9, 13, 21, and 25; and BMP values from visit 1 to visit 25. As primary outcome, we will use the covariance analysis model that includes each group as a fixed factor, ADAS-cog, K-BDI, BAQ, DMTS scores and HRV, BPM, and fNIRS values as dependent variables, and differences in demographic characteristics as covariates. A paired *t* test or Wilcoxon signed-rank test will be performed on the same participant on the secondary outcome before and after treatment in each group.

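### The 2-hour cigarette and caffeine notice first appears at visit 1, so the baseline of every HRV change endpoint is not shown to be under the control that applies to later values

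*Protocol article*

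**What the plan says.** Section 2.4 (Study procedure) describes the trial visit by visit. Its screening paragraph lists vital signs, demographics, history, examination, laboratory tests and electrocardiogram, and ends with participants receiving a schedule of visits. Cigarettes and caffeine are not mentioned there, nor in section 2.3.2 (Screening).

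The visit 1 paragraph sets out the tests and then the treatment session, during which HRV is taken: "In the meantime, the investigator will check the subject's BPM and HRV". The next sentence deals with side effects and other drugs, and also has the investigator "inform them that cigarettes and caffeine must be avoided 2 hours before the test, as they affect the HRV". For visits 2 to 24 the step is repeated: "The investigator will check the subject's adverse reactions and concomitant medications and inform them in the same manner as on visit 1".

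Table 1 has a row named "Education of visit schedule", marked at screening and at every visit, with no description of its content.

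Section 2.9.2 (Secondary outcomes) defines the HRV endpoints as changes in "HRV values from visit 1 to visit 5, 9, 13, 21, and 25". Two analyses apply to them. Between arms, "we will use the covariance analysis model that includes each group as a fixed factor". Within arms, "A paired *t* test or Wilcoxon signed-rank test will be performed on the same participant on the secondary outcome before and after treatment in each" (meaning each arm).

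**The concern.** The protocol chose this restriction itself and gave the reason for it: the two exposures affect HRV. A restriction covering the two hours before a recording works only if the participant hears of it before travelling to the visit. The text places it first at the visit whose HRV is the reference for all five change endpoints.

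If the procedure is followed as written, a participant who smokes or drinks coffee may arrive at visit 1 uninstructed and arrive instructed at visits 5, 9, 13, 21 and 25. That participant's change score then contains a move from uncontrolled to controlled exposure as well as any treatment effect. A within-arm before/after test has no comparison group to cancel such a shift, so it can be read as an effect of treatment. An uncontrolled baseline also cannot be repaired later, because there is only one visit 1.

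**Working it through.** **Order of procedures.** No figure in the plan bears on this point, so the main check is to set the sections side by side.

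| Occasion | HRV recorded? | Notice stated before that occasion? | Role in the endpoints |
|---|---|---|---|
| Screening | No (Table 1) | – | none |
| Visit 1 | Yes, during the session | None stated | baseline for all five changes |
| Visits 5, 9, 13, 21 | Yes | Yes, at visit 1 and each visit since | follow-up values |
| Visit 25 | Yes (Table 1) | Yes, at visits 1 to 24 | follow-up value |

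The order of sentences within the visit 1 paragraph does not decide the matter. Even a notice given on arrival at visit 1 could not secure two hours of abstinence before a recording made in that visit. The asymmetry thus depends only on whether participants are told before visit 1, and the text states no such step.

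**Which analyses are exposed.** Let p be the share of participants exposed within two hours of visit 1, d the acute shift in HRV in SD units, and r the correlation between two HRV values of the same participant. Assume no treatment effect, full compliance once instructed, and one direction of shift for both exposures. Then:

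- mean spurious change in an arm = p × d
- SD of change = √(2(1 − r) + p(1 − p)d²)
- noncentrality of the paired t test = √n × mean / SD, with n = 22 per arm (all randomised, no dropout)

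None of p, d or r is in the documents. The values below are assumptions chosen to show the range; rejection rates are two-sided at 5%.

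| p | d | r | Mean change (SD units) | SD of change | Noncentrality | Rejection rate |
|---|---|---|---|---|---|---|
| 0.1 | 0.3 | 0.6 | 0.03 | 0.899 | 0.16 | 5.3% |
| 0.3 | 0.3 | 0.6 | 0.09 | 0.905 | 0.47 | 7.3% |
| 0.5 | 0.4 | 0.7 | 0.20 | 0.800 | 1.17 | 20% |
| 0.7 | 0.5 | 0.8 | 0.35 | 0.673 | 2.44 | 64% |

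The direction is clear: if exposure is more common before visit 1 than later and shifts HRV on average, the within-arm test rejects more often than its nominal level. The size runs from negligible to severe, depending wholly on the assumed inputs.

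**Between arms.** Both arms receive the same notice at the same point, so under randomisation the expected shift p × d is the same in each and their difference has expectation zero. What remains is the extra term p(1 − p)d² in the variance of change. In the third row, the SD of change rises from √(2 × 0.3) = 0.775 to √(0.6 + 0.25 × 0.16) = 0.800, about 3%. This is a loss of precision, not a bias.

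**The case against.** The strongest objection is that the absence of an earlier notice is inferred from silence. The article nowhere says that participants first hear of the restriction at visit 1, or that nothing is said at screening. The screening list in section 2.4 is demonstrably incomplete: it omits MoCA-K and drug history, both of which Table 1 marks at screening. The education row in Table 1 is also marked at screening without saying what it covers. And the article condenses a fuller protocol (version 1.3), where a participant instruction of this kind might stand. All of this holds. It means the documents do not establish that the baseline is taken without the control, only that the control is not shown to apply to it.

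It does not dispose of the point. The article does not leave the notice out; it assigns it to a visit, and at that visit it cannot serve its stated purpose for that visit's recording. The education row is named for the visit schedule, and nothing links it to abstinence.

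A reader might also infer that every HRV change score is contaminated, or that the comparison of the two treatments is biased. The documents support neither. Participants not exposed before visit 1 are unaffected, and the arms are handled alike. A chance imbalance between arms in smokers or coffee drinkers is already reflected in the standard error of the comparison. Finally, the within-arm tests cannot separate treatment from the passage of time in any case, which limits what rests on them.

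**Conclusion.** The point holds in a limited form. As written, the notice first appears at the visit that supplies the baseline for all five HRV change endpoints, so that baseline is not shown to be under the control that applies to later values. Among participants exposed before visit 1 this can shift HRV change in both arms. The planned within-arm paired tests are open to bias; the between-arm covariance analysis gains noise only.

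The size cannot be derived from the documents. The rejection rates of about 5% to 64% are illustrations under outside assumptions and should not be read as an estimate. The conclusion also assumes that no earlier notice is given in documents not shown; if one is, only a clarification is needed. HRV is one of seven secondary outcomes in a pilot trial, and the primary MoCA-K analysis is unaffected.

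**What to change.** 1. In section 2.4 and in the screening column of Table 1, state that the 2-hour cigarette and caffeine notice is given at screening, before visit 1. If this is already done, say so.
2. Before the visit 1 recording and before each HRV endpoint recording (visits 5, 9, 13, 21 and 25), record with a yes/no item whether abstinence was kept.
3. Use that item in a sensitivity analysis of the HRV endpoints that excludes non-adherent recordings.

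The cost is one sentence moved or added and one extra item on the case report form. There is no need to delay the visit 1 session for a participant who did not abstain, since the recorded answer allows that value to be handled in the analysis.

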### Intervention

2.5

Participants in the control group will visit twice a week for 12 weeks, for a total of 24 visits, to receive acupuncture treatment. Participants in the intervention group will also visit twice a week for 12 weeks, for a total of 24 visits, and receive combined NF-acupuncture treatment. Acupuncture treatment will be performed while abiding by the Standards for Reporting Interventions in Controlled Trials of Acupuncture.^[25]^

#### Acupuncture method

2.5.1

GV 20, EX-HN1, LI4, and ST36 (total of 9 points) will be selected as intervention points according to their internal agreement with the acupuncture rationale. The specific operation method will be as follows: the subject sits with their back on the bed to conduct NF training or simple EEG together; the needle is inserted perpendicular to the skin at a depth of 5 to 30 mm; Korean Medical Doctor will leave the intervention room after acupuncture in order to blind NF intervention and return to the room 30 minutes later to remove needles.

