#### NF training method

2.5.2

The intervention group will perform the NF sensorimotor rhythm (SMR) training protocol, whereas the control group will have EEG measured for the 30 minutes of acupuncture treatment.

The ProComp 2 Neurofeedback system (Promp Infiniti 8 channel system, Model NO. BA500, Thought Technology Ltd., Quebec, Canada) will be used in this trial. After cleaning the electrode location with an abrasive conductive gel (Nuprep, Weaver and company, CO) and filling the electrode cups with conductive gel (ten 20 conductive paste, Weaver and Company, CO), an electrode will be placed at the subject's central scalp area according to the international 10/20 system. A reference and ground electrode will be placed on the left and right earlobes, respectively. A 3-electrode location input impedance will be maintained under 5 kΩ.^[26]^

The training session will consist of a 6-minute baseline trial and a 30-minute NF training trial, divided into 6 segments. To determine threshold values, each subject will be measured at baseline SMR wave (12–15 Hz, low beta waves) for 3 minutes with eyes closed and 3 minutes with eyes open. NF training, which is designed to increase threshold SMR values, will be performed 6 times for 5 minutes with 20 to 30 seconds of rest between each trial. BPM and HRV values will also be collected in each trial. The threshold value at each trial is newly set according to the subject's feedback.

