### Randomization, blinding

2.7

The investigator in charge of randomization, who will not be involved in the trial, will generate the random sequence list using SAS Version 9.4 (SAS Institute. Inc., Cary, NC) program, and each randomized code will be kept in sealed envelopes, to be managed by the PI. For randomized allocation, the stratified block randomization method will be used, for which the stratification factors will be gender and age. This method involves stratification into 4 subgroups, by age and gender: 1 group of 50 to 60 years old individuals and 1 of 61 to 75 years old individuals for each gender. The investigator assigning the randomization code will open the sealed envelope in front of the participants to whom the identification code is assigned. This investigator will record the date of opening, sign the envelope, and store it separately.

In this trial, blinding of the subjects is not possible; assessor blinding will therefore be performed to control for bias. An investigator doctor not involved in randomization will perform acupuncture on subjects before NF training or simple EEG, will be blinded to the type of treatment to be administered, and will subsequently perform an evaluation of the effectiveness and safety.

Blinding breaking should be determined on a case-by-case basis and considered only in serious medical emergencies. If the investigator determines that blinding breaking is necessary, they can contact the PI or sponsor to obtain consent, and subsequently document the breaking procedure.

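### Assessor blinding, the trial's only blinding, is not secured by the procedure as written: the doctor who needles also rates outcomes, and may re-enter while neurofeedback is still running

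*Protocol article*

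**What the plan says.** Section 2.7 of the protocol article (Randomization, blinding) states that "blinding of the subjects is not possible; assessor blinding will therefore be performed to control for bias". The person meant to be blind is the doctor who performs the acupuncture. This doctor takes no part in randomization, "will be blinded to the type of treatment to be administered, and will subsequently perform an evaluation of the effectiveness and safety".

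Section 2.5.1 (Acupuncture method) gives the mechanism. After inserting the needles the doctor leaves the room, "in order to blind NF intervention and return to the room 30 minutes later to remove needles".

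Two sections time what happens during that absence in the experimental arm:

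- Section 2.5.2 (NF training method): "The training session will consist of a 6-minute baseline trial and a 30-minute NF training trial, divided into 6 segments". The training itself "will be performed 6 times for 5 minutes with 20 to 30 seconds of rest between each trial".
- Section 2.4 (Study procedure): "5 times for 5 minutes, 30–60 seconds of rest between each trial". The same sentence gives the intervention group's acupuncture as lasting one minute, against 30 minutes for the control group.

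In the control arm, section 2.5.2 limits the EEG to the 30 minutes of needling. Both arms have 24 treatment visits (section 2.2).

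**The concern.** The blind depends on one condition: the doctor must not see anything that distinguishes neurofeedback from a plain EEG recording. The only stated protection is a 30-minute absence, and on the fuller of the two schedules the neurofeedback does not fit into 30 minutes. The control recording does. An active session at re-entry would then point to the experimental arm.

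The same doctor is also the treating clinician of a participant who knows the allocation. Adverse events are asked about at each visit (section 2.9.3) and graded for causality to the intervention (section 2.9.4), and section 2.7 gives the safety evaluation to this doctor. Such conversations are a second route by which the arm could become known, whatever the timing.

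At stake are the visit 25 MoCA-K, which is the primary outcome, together with ADAS-cog and the causality grading of adverse events. If the rater knows the arm, a difference between groups cannot be cleanly separated from the rater's expectation, and no analysis can repair that afterwards.

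**Working it through.** **Inputs**

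- Doctor's absence: 30 min (section 2.5.1).
- Section 2.5.2: 6 segments of 5 min, rests of 20 to 30 s between them, and a 6-min baseline.
- Section 2.4: 5 segments of 5 min, rests of 30 to 60 s between them, and no baseline mentioned.
- Control EEG: 30 min (section 2.5.2).

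**Formula:** duration = segments × 5 min + (segments − 1) × rest, plus the baseline where it applies.

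**The plan's own figure.** 6 × 5 = 30 min reproduces the stated training time of 30 min, but only with the rests and the baseline left out.

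**Section 2.5.2 in full**

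- Training with rests: 30 + 5 × 20 s = 31.7 min, to 30 + 5 × 30 s = 32.5 min.
- With the baseline inside the absence: 31.7 + 6 = 37.7 min, to 32.5 + 6 = 38.5 min.

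**Section 2.4**

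- Training with rests: 25 + 4 × 30 s = 27 min, to 25 + 4 × 60 s = 29 min.

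**Against re-entry at 30 min**

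| Schedule | Duration (min) | Relative to re-entry |
|---|---|---|
| 2.5.2, baseline before needling | 31.7–32.5 | still running, by 1.7–2.5 min |
| 2.5.2, baseline during the absence | 37.7–38.5 | still running, by 7.7–8.5 min |
| 2.4 as stated | 27–29 | ended 1–3 min earlier |
| Control EEG | 30 | ends at re-entry |

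Section 2.7 places needling before the neurofeedback, and section 2.5.2 counts the baseline as part of the training session. This favours the second row but does not settle it, because neither section says whether the baseline precedes needling.

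The two neurofeedback schedules differ in both segments and rests, so they cannot both describe the trial. The one-minute acupuncture in section 2.4 also does not fit section 2.5.1, where the needles stay in until the doctor returns after 30 minutes.

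**The case against.** The protocol clearly intends a blind: the doctor is kept out of randomization and leaves the room for that purpose. Both arms are connected to EEG equipment, and nothing is said about what can be seen or heard at re-entry. The screening MoCA-K precedes allocation, so for the primary outcome only the visit 25 rating is exposed. This is also a 44-person pilot. All of this stands, and it limits how far the point can be taken.

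Four stronger readings are tempting, and the documents do not support them.

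- **That the blinding fails.** A reader might infer this from the overrun. Unmasking depends on what is visible at re-entry, which is not described, and on the section 2.4 schedule the training has already ended.
- **That most readings of the timing overrun.** Adding the 6-minute baseline to the section 2.4 schedule gives 33 to 35 minutes, but that combines two sections in a way neither states.
- **That the rater has 48 contacts with each participant before the primary rating** (24 visits, insertion and removal). This assumes one doctor attends every visit, which is not stated, and contact is not the same as unmasking.
- **That the bias can be sized and favours the combined treatment.** Setting an assumed 0.2 to 0.3 SD against the planned effect size of 0.8 gives a percentage (25 to 38%), but neither that assumption nor the direction has a source in the documents.

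What the objection does not remove is that the treating doctor is the named assessor, and that the one stated safeguard conflicts with one of the article's two session schedules.

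**Conclusion.** The point holds in this form: the assessor blind is not secured by the procedure as written. Following section 2.5.2 literally, neurofeedback is still running when the doctor returns, by 1.7 to 2.5 minutes, or by 7.7 to 8.5 minutes if the baseline falls inside the absence. The control recording ends at 30 minutes, so the difference can reveal the arm, and this can recur over 24 visits. Section 2.4 contradicts this schedule, and on its timing the problem at re-entry does not arise. The rater's role as treating doctor of unblinded participants remains in either case.

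The conclusion assumes that the doctor's 30 minutes start when neurofeedback, or its baseline, starts; any set-up time in between would lengthen the overrun. It also assumes that an active session can be recognised on entering the room. The resulting bias in MoCA-K, in size and direction, cannot be derived. This should be fixed, but it does not show that the trial's result would be invalid.

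**What to change.** 1. Reconcile sections 2.4, 2.5.1 and 2.5.2: the number of segments, the rests, the place of the baseline, the duration of acupuncture in the intervention group and the time of re-entry. The result should be that neurofeedback and control EEG have both ended, and the arms look the same, whenever the doctor re-enters. Which session and needling times are right is for the sponsor to decide.
2. Where an existing investigator who did not treat that participant and does not know the allocation is available, have that person rate MoCA-K and ADAS-cog at visit 25.
3. Where no such person is available, tell participants not to disclose their arm, record the rater's guess of the arm at visit 25, report it with the result, and describe the assessor as the treating doctor.

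The first item costs wording. The second costs scheduling at visit 25, and is cheap only if a suitable investigator already exists; the article does not say how many doctors take part. The third costs an instruction to participants and one case report form item.
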